**Methods/design:**

614 adult female patients will be recruited from four primary care research networks (Wales, England, Spain, the Netherlands) and individually randomised to either POCT guided care or the guideline-informed ‘standard care’ arm. Urine and stool samples (where possible) will be obtained at presentation (day 1) and two weeks later for microbiological analysis. All participants will be followed up on the course of their illness and their quality of life, using a 2 week self-completed symptom diary. At 3 months, a primary care notes review will be conducted for evidence of further evidence of treatment failures, recurrence, complications, hospitalisations and health service costs.

The primary objective is to compare appropriate antibiotic use on day 3 between the POCT and standard care arms using multi-level logistic regression to produce an odds ratio and associated 95% confidence interval. Costs of the two management approaches will be assessed in terms of the primary outcome.

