##### Randomisation

The randomisation and allocation of eligible participants will be undertaken as part of the data collection process. Whilst completing the baseline CRF, clinicians will be asked to randomise the patient using a password protected POETIC randomisation website. Each practice will be allocated unique login details to the website. The clinician will enter the relevant data into the website, including the required stratifying and balancing variables, which include centre and practice details, and number of presenting symptoms (dysuria, frequency, urgency). The patient must present with at least one of these in order to be eligible for the trial. Once all relevant data has been entered, the randomisation programme will provide the trial allocation for that participant (either Standard care or POCT arm). This information will be recorded on the baseline CRF.

There is no credible blinding mechanism that can be utilised in this trial. Immediately after receiving the allocation, the clinician will need to be aware of the result of the randomisation so as to know whether to use the point of care test or not, and the participant will be need to made aware as they may need to receive a new prescription 24 hours after initial diagnosis, once the POCT results are made available to the clinician.

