### Analysis

#### Sample size calculation

A total of 614 participants (approximately 154 per network; 307 per arm) are required. We aim to improve appropriate antibiotic prescribing by at least 20% from an expected level of 55%. However, our sample size calculation is based on detecting a difference of 15 percentage points difference from control (i.e. from 55% to 70%). We need a total sample of 460 (230 for each arm) patients for final analysis (significance level α = 0.05, statistical power (1-β) = 0.90) and will recruit 614 patients to allow for a 25% loss to follow up (which requires a first urine and also follow-up via diary or telephone interview).

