#### Statistical analysis

The primary outcome will be appropriate antibiotic use on day 3 (with day 1 being the day that the patient consulted with their primary care clinician). For women who are shown to have a UTI, appropriate antibiotic use on day 3 will be defined as use of an antibiotic for which the isolated pathogen has been shown to have in vitro sensitivity (based on laboratory analysis). For women who do not have a UTI, appropriate antibiotic use on day 3 will be defined as no antibiotic use on this day.

The analysis of this primary outcome will be intention-to-treat and will be undertaken utilising a multi-level logistic regression. Whilst this is an individually randomised controlled trial we will use multi-level modelling with patient as the 1^st^ level and practice as the 2^nd^ level, plus we will test for clustering at the clinician level as the outcome could be seen as a clinician behavioural measure. Country will be used as a fixed level covariate at the practice level.

Secondary outcomes will be analysed using multi-level logistic or linear regression as appropriate, except for symptoms/recovery (daily symptom score), which will be modelled over time to allow for the correlation structure between scores on different days.

This trial is not powered for any sub-group analysis, and no interim analysis is planned. Some exploratory sub-group analysis will be done by country, number of symptoms and recent antibiotic history, using the relevant variables to form an interaction term with arm in the model.

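### The primary model does not name number of presenting symptoms, although the randomisation balances on it; if that variable is prognostic, inference is slightly conservative

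*Protocol article*

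**What the plan says.** The Randomisation section has the clinician enter the "stratifying and balancing variables, which include centre and practice details, and number of presenting symptoms" before the website returns the allocation.

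Under Statistical analysis, the primary outcome is analysed by intention to treat using "multi-level modelling with patient as the 1^st^ level and practice as the 2^nd^ level". Clustering by clinician is to be tested. The covariate statement is "Country will be used as a fixed level covariate at the practice level".

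Symptom number appears once more in that section: "Some exploratory sub-group analysis will be done by country, number of symptoms and recent antibiotic history", each as an interaction with arm. The abstract gives the effect measure, "using multi-level logistic regression to produce an odds ratio and associated 95% confidence interval".

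Of the three randomisation variables, practice is therefore in the stated model and centre is there through country. Number of presenting symptoms is not named.

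**The concern.** When allocation is balanced on a prognostic variable, the two arms cannot differ by chance on it. An analysis that ignores the variable still counts that chance difference as part of the error. Its model-based standard error is then larger than the true spread of its estimate over repeated trials, so p-values are somewhat too large and some power is lost. In a logistic model the unadjusted odds ratio is also closer to 1 than the one conditional on the variable.

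The article is specific about the model: it gives the levels, the clustering test and a covariate. Someone fitting it as written would leave out a variable that the trial collects before allocation and uses to constrain it.

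**Working it through.** **Inputs from the article (Sample size calculation).** 55% versus 70% appropriate use, α = 0.05, power 0.90, 230 per arm analysed, 25% loss, 614 recruited.

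**Inputs assumed.** The article gives neither the distribution of symptom number nor its link with the outcome. I take 20%, 35% and 45% of women with 1, 2 and 3 symptoms, exact balance within each level, no practice or country effects, and an odds ratio per extra symptom of 1, 1.5, 2 or 3. The overall rates are held at 55% and 70%.

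**Step 1: the plan's own figure.** Two-sided, pooled variance:

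n = [1.960·√(2·0.625·0.375) + 1.2816·√(0.55·0.45 + 0.70·0.30)]² / 0.15² = (1.3419 + 0.8668)² / 0.0225 = 216.8, so 217.

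With continuity correction: (216.8/4)·[1 + √(1 + 4/(216.8·0.15))]² = 230. Then 460/0.75 = 613.3, so 614. Both stated figures reproduce.

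**Step 2: standard error reported by the model without symptom number.**

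√[1/(230·0.55·0.45) + 1/(230·0.70·0.30)] = √(0.01757 + 0.02070) = 0.1956. This does not depend on how prognostic symptom number is.

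**Step 3: true SD of that estimate under balanced allocation.** Only the variance within symptom levels remains. Let V be the weighted mean of p(1−p) over the three levels in an arm, and P the overall rate in that arm. The SD is √[Σ V / (230·{P(1−P)}²)], summed over arms.

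Example at odds ratio 2: control rates are 34.1%, 50.9% and 67.5%, giving V = 0.2311; POCT rates are 50.8%, 67.4% and 80.5%, giving V = 0.1975. SD = √[0.2311/(230·0.2475²) + 0.1975/(230·0.21²)] = √(0.01641 + 0.01948) = 0.1894. The ratio is 0.1956/0.1894 = 1.033.

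**Step 4: type I error without symptom number.** Both arms are set to 55%, so the ratio is √(0.2475/V) and the error is 2Φ(−1.96·ratio). At odds ratio 2: √(0.2475/0.2311) = 1.035, giving 4.3%.

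**Step 5: power.** Without symptom number: Φ[(0.6466 − 1.96·0.1956)/SD], where 0.6466 is the log of the overall odds ratio 1.91. With it: Φ(d/SE − 1.96), where d is the conditional log odds ratio. Its SE is 1/√Σ[W₀W₁/(W₀ + W₁)], where W₀ and W₁ are the control and POCT values of n·p(1−p) within each symptom level.

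| OR per extra symptom | True SD | Model SE / true SD | Type I error, not adjusted | Power, not adjusted | Power, adjusted | Adjusted log OR (SE) |
|---|---|---|---|---|---|---|
| 1 | 0.1956 | 1.00 | 5.0% | 91.1% | 91.1% | 0.647 (0.196) |
| 1.5 | 0.1935 | 1.01 | 4.7% | 91.3% | 91.6% | 0.662 (0.198) |
| 2 | 0.1894 | 1.03 | 4.3% | 91.8% | 92.6% | 0.691 (0.203) |
| 3 | 0.1810 | 1.08 | 3.4% | 92.7% | 94.4% | 0.758 (0.213) |

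**Step 6: cross-check by simulation.** Logistic fits to 5,000 simulated trials per scenario gave power without and with symptom number of 91.5% and 91.8% (odds ratio 1.5), 92.6% and 93.7% (2), and 93.2% and 95.1% (3), with Monte Carlo error of about 0.4 point. The gain is again about 0 to 2 points. With equal thirds in the three symptom levels instead of 20/35/45%, the Step 3 ratios are 1.012, 1.035 and 1.085.

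**The case against.** The strongest objection is scope. This is a condensed article and the SAP is not shown. The text says that country will be used; it does not say that nothing else will be. The SAP may already contain symptom number. That limits the weight of the point. It does not remove it, because the model that is stated does not match the randomisation that is stated.

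The second objection also stands: nothing in the article shows that symptom number predicts the outcome. One might argue that it predicts both infection and prescribing, and hence appropriate use. But appropriate use means an active antibiotic if there is a UTI and no antibiotic if there is not, so the two parts can offset each other. As an illustration with assumed figures, take UTI in 30/45/60% of women with 1/2/3 symptoms, antibiotic use in 60/75/90% independently of UTI, and 85% susceptibility. Appropriate use is then 0.30·0.60·0.85 + 0.70·0.40 = 43%, and by the same formula 42% and 50%. That gradient is weak, and the loss would be negligible.

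Four stronger readings are tempting and are not supported:

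- **Power falls below 90%.** A simulation that fixes an odds ratio of 1.91 within equal-sized symptom levels can show power of 0.891 or 0.862. With control rates of 39/55/70% or 33/55/75%, however, the overall difference is only 14.2 or 13.5 points, not the planned 15. Part of that drop is a smaller effect.
- **Adjustment narrows the interval.** On the log odds ratio scale the adjusted standard error is larger. Power rises because the conditional estimate is larger.
- **The unadjusted odds ratio is biased.** It is a marginal quantity and a different estimand.
- **Country fails to represent centre.** The Trial design section lists Wales, England, the Netherlands and Spain as the four countries, which match the four networks. The three-way grouping elsewhere concerns test plates and guidelines.

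**Conclusion.** The mismatch between randomisation and primary model holds; its consequence is small and conditional. At an odds ratio of 1.5 per extra symptom or less it is negligible. At 2 to 3 the unadjusted standard error is about 3% to 8% too large for its own estimate, type I error is about 4.3% to 3.4%, and about 1 to 2 points of power are forgone. The trial keeps more than its planned 90% power throughout, the required sample size does not change, and inference errs on the cautious side.

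These sizes rest on the assumed symptom distribution and odds ratios, exact balance, and no practice or country effects. Severity is minor.

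**What to change.** State the primary model as multi-level logistic regression with fixed effects for arm, number of presenting symptoms (1, 2 or 3, categorical) and country (Wales, England, Spain, Netherlands), and a random intercept for practice. Keep the symptom-by-arm interaction as an exploratory analysis. Say in the same place that the reported odds ratio is conditional on symptom number. Readers should then expect a value somewhat further from 1, with a larger standard error, than the marginal 1.91 implied by 55% versus 70%.

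The cost is one sentence. The variable is entered on the randomisation website before allocation, so it adds no data collection. Fixing the covariate in advance also removes a later choice between adjusted and unadjusted results in an unblinded trial. If the SAP already lists it, nothing further is needed.

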#### Economic evaluation

All resources will be valued using standard methods. Results will be reported as mean total cost (including the cost of the POCT for those in the POCT arm) per unit increase in appropriate antibiotic prescribing. Since appropriate prescribing may reduce total antibiotic dispensing and subsequent health care consulting, the intervention may be shown to dominate best practice usual care i.e. have lower cost and greater effect, in which case it will be unambiguously more cost effective. In the event of non-dominance (higher cost/greater effect) results will be reported in the form of an incremental cost effectiveness ratio (ICER) showing the extra cost per unit improvement in appropriate prescribing.

Uncertainty in any parameters will be assessed through a series of one way sensitivity analyses. Non-parametric bootstrapping using 10,000 replications will be applied to cost and effect data for both groups. A two-dimensional cost-effectiveness plane will show the uncertainty in costs and effects through a cost-effectiveness ellipse. A cost effectiveness acceptability curve will show the probability of the intervention having an incremental cost effectiveness ratio below a range of acceptability thresholds [11].

## Discussion

The POETIC trial will be the first to evaluate the diagnostic performance cost effectiveness of a POCT (Flexicult™) for the diagnosis and management of uncomplicated UTI in primary care. The appropriateness of antibiotic prescribing will be compared between patients managed with the aid of Flexicult™ POCT and patients managed according to guideline informed usual care. The Flexicult™ POCT offers the advantage of quantifying bacterial growth, organism identification and antibiotic sensitivities within 24 hours at the point of care, and may therefore be a useful adjunct to improving the antimicrobial management of UTI in primary care. Flexicult™ is already in everyday, widespread use in Danish primary care, despite it never have been subject to a clinical trial to determine its cost effectiveness. Few POCTs have been subjected to rigorous pragmatic clinical trials that evaluate not only diagnostic performance but also cost effectiveness using a range of outcomes including patient orientated measures.

As resources for health care are universally scarce, the economic evaluation will assess the cost of any benefits achieved through the use of the POCT. In addition to the direct costs associated with use of the technology this will include any savings (or additional costs) which result from more appropriate diagnosing of UTI. This will provide additional important information to health care providers and funders to aid them in making the most efficient use of their finite resources.

The analyses proposed in POETIC will generate much needed evidence that should therefore reduce equipoise about the use of this POCT in managing a common condition. If shown to be cost effective, the use of this POCT could benefit individual sufferers and provide evidence for health care authorities to develop evidence based policies to combat the spread and impact of the unprecedented rise of infections caused by multi-drug resistant-gram negative bacteria (MDR-GNB) in Europe. If shown to be not clinically and cost effective, then that too will provide evidence to change practice where it is currently used, and re-focus research efforts on developing alternative pathways for improving the management of patients presenting in primary care with symptoms attributable to UTI.

## Abbreviations

CFU/mL: Colony Forming Units per millilitre
CI: Confidence interval
CRF: Case report form
GCP: Good clinical practice
GP: General practitioner
MALDI-TOF: Matrix assisted laser desorption/ionization - time of flight mass spectrometry
MIC: Minimum inhibitory concentration
MSU: Mid-stream urine
OR: Odds ratio
PIL: Participant information leaflet
POCT: Point of care test
QoL: Quality of life
REC: Research Ethics Committee
SOP: Standard operating procedure
UKECA: United Kingdom Ethics Committee Authority
UTI: Urinary tract infection
